## Current study status

The ON-TRK study is currently recruiting patients and as of November 2021, 22 patients have been enrolled. The study has an estimated primary completion date of November 2029 and an estimated study completion date of March 2030 [35]. To date, numerous study sites currently recruiting are in Belgium, Canada, Germany, Sweden, Switzerland, and the USA; other study sites and countries will be recruited to participate in the study when local approval and reimbursement for larotrectinib are granted if deemed relevant for the completion of the study (https://clinicaltrials.gov/ct2/show/NCT04142437).

## Discussion

An improved understanding of the mechanisms that drive tumorigenesis has led to substantial advances in the treatment of cancer; however, an unmet need for highly effective and well-tolerated therapies remains, particularly in the metastatic setting and in rare tumors. Identification of recurrent oncogenic drivers has led to a precision medicine approach in which specific genetic alterations are targeted by selective agents. Furthermore, emerging evidence suggests that certain genomic alterations are present as primary oncogenic drivers across a wide variety of different tumor types, providing the rationale for a tumor-agnostic treatment approach. The larotrectinib development program was designed with such an approach, with the aim of demonstrating the activity and safety of larotrectinib in a wide variety of tumor types. As such, no central pathological review is planned given that there is less emphasis on the tumor-specific details.

The FDA Accelerated Approval Program was initiated to allow for earlier approval (and patient access) of drugs that treat serious conditions and fill an unmet medical need, based on a surrogate endpoint. Drugs which receive accelerated approval under this program are required to be further studied in phase IV confirmatory trials.

Larotrectinib was granted accelerated approval based on data from three phase I/II single-arm studies, but safety data are relatively limited, particularly with respect to patient numbers and long-term exposure. ON-TRK is the first prospective, non-interventional study of a TRK inhibitor designed to support the conversion of an accelerated approval to a full approval. The study will provide further evidence to support the safety and effectiveness of larotrectinib in patients with locally advanced or metastatic TRK fusion cancer in real-world practice conditions. Larotrectinib was granted accelerated approval contingent upon fulfilling post-approval requirements in order to obtain full approval. One such requirement is to evaluate an adequate number of patients to characterize response and durability of response for each of the following tumor types: CNS tumors, colorectal cancer, melanoma, and non-small cell lung cancer (NSCLC). A minimum of 40 patients with cancers other than CNS tumors, colorectal cancer, infantile fibrosarcoma, melanoma, NSCLC, salivary cancers, soft tissue sarcoma, and thyroid cancer (e.g., biliary tract cancers, breast cancer, cholangiocarcinoma, gastrointestinal stromal tumors) will also be studied. Evaluating response in these tumor types will further support the tumor-agnostic designation of larotrectinib and may enable additional subgroup analysis by primary tumor type. Another requirement is to conduct a study of larotrectinib following an adequate number of pediatric patients with TRK fusion cancer for 5 years to evaluate the risk of potential long-term adverse effects of larotrectinib on their growth and development; this is covered as a secondary objective of ON-TRK. Patients will be evaluated for age-appropriate growth and developmental milestones and undergo neurological examination at suitable intervals (such as every 6 months) until larotrectinib is discontinued or for at least 5 years, whichever occurs first. In describing AEs requiring dose modifications, ON-TRK will also fulfill another requirement, which is to assess any unexpected risks of SAEs in patients requiring a third dose modification of larotrectinib due to toxicity. An adequate number of adult or pediatric patients with a body surface area of at least 1.0 m^2^ requiring a third dosage modification due to a treatment-related AE will receive larotrectinib 100 mg orally once daily to better describe the tolerability of this approved dosage modification for larotrectinib. The following information will be collected from each patient: age and body surface area (if pediatric), treatment-related AEs leading to the first and second dose reductions of larotrectinib, duration of treatment on prior dose levels, duration of treatment at the 100-mg oral once-daily regimen, best overall response and DOR, and tumor information collected while receiving the 100-mg oral once-daily regimen. An additional request from the FDA was to assess effectiveness by an IRC in this non-interventional study.

Additional trials are ongoing in specific populations of patients with TRK fusion cancer that will gather additional safety and efficacy data for larotrectinib. Recruitment is currently ongoing for the phase II NAVIGATE basket trial (NCT02576431) for patients with kidney cancer, squamous cell cancer of head or neck, ovarian solid tumors, melanoma, non-secretory breast cancer, and colorectal cancer harboring *NTRK* gene fusions. The phase II MATCH screening trial (NCT02465060) is studying the efficacy of various treatments (including larotrectinib) directed by genetic testing work in adult patients with solid tumors or lymphomas with progression following at least one line of standard treatment, or for which there are no approved or standard therapies. The phase II pediatric MATCH screening and treatment trials (NCT03155620 and NCT03213704) are similarly studying the effectiveness of treatment directed by genetic testing in pediatric patients with solid tumors, non-Hodgkin lymphomas, or histiocytic disorders that have either progressed following at least one line of standard systemic therapy and/or for which no standard treatment exists that has been shown to prolong survival. Another phase II trial (NCT03834961) is evaluating the efficacy and safety of neoadjuvant larotrectinib in pediatric patients with previously untreated TRK fusion solid tumors (including infantile fibrosarcoma) or relapsed TRK fusion acute leukemia. A study with more than 15 years’ follow-up of childhood cancer survivors who received larotrectinib will also be needed to determine if there is a potential longer-term risk of adverse effects of larotrectinib on growth and development.

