**Methods:**

ON-TRK is a prospective, non-interventional, open-label, multicenter, multi-cohort, post-approval study in adult and pediatric patients with locally advanced or metastatic TRK fusion cancer treated with larotrectinib that will describe the safety and effectiveness of larotrectinib in real-world practice conditions. Adult patients will be grouped by tumor type and followed for at least 2 years. Patients < 18 years old will be enrolled under a ‘pediatric’ cohort regardless of tumor type and will be followed for 5 years to evaluate the risk of potential long-term adverse effects of larotrectinib on their growth and development. The effectiveness of larotrectinib in the overall study population as well as in patient subgroups will also be evaluated. Procedures avoided in patients with infantile fibrosarcoma (e.g., amputation) and the number of patients who were able to undergo surgery with a curative intent (excluding amputation) because of the use of larotrectinib will be described. Larotrectinib treatment patterns in real-world practice, including dosing and duration of treatment, will be described.

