Results from these clinical trials demonstrated that in addition to having tumor-agnostic activity, larotrectinib is also effective across age groups, including in children and adolescents. Of the 159 patients analyzed in the integrated dataset, 52 (33%) were aged < 18 years old [29]. Tumor types included infantile fibrosarcoma (56%), other soft tissue sarcoma (37%), thyroid (4%), congenital mesoblastic nephroma (2%), and melanoma (2%). ORR was 92%; at the time of data analysis, medians for DOR, PFS, and OS were not reached. With the duration of treatment ranging from 1.3 + to 34.0 + months, larotrectinib was well tolerated with low rates of discontinuation due to treatment-related AEs and low rates of neurologic AEs.

Longer-term safety evaluation is required, and this is particularly relevant for pediatric patients in order to investigate potential developmental effects of treatment. There are limited available data on the safety profile of larotrectinib in a broader population and over a longer time period. Real-world safety and effectiveness data in a larger patient population are needed with a longer-term follow-up. The ON-TRK study is a prospective, open-label, multicenter, multi-cohort, non-interventional study in patients with locally advanced or metastatic TRK fusion cancer treated with larotrectinib. The aim of the ON-TRK study is to describe the safety and effectiveness of larotrectinib in this patient population under real-world conditions in standard clinical practice. As it is a post-approval safety study, it is also designed to fulfill FDA requirements for the accelerated approval of larotrectinib, which include additional studies to validate and describe the clinical benefits of larotrectinib. Post-approval commitments set forth in the FDA’s accelerated approval of larotrectinib require enough pediatric patients be followed for 5 years to evaluate the risk of potential long-term adverse effects of larotrectinib on growth and development and the assessment of unexpected risks of serious AEs (SAEs) in patients requiring a third larotrectinib dose modification due to toxicity [30]. This study is also intended to fulfill the post-marketing requirements set forth by the regulatory bodies of Canada and South Korea, and is part of the risk management plan provided to the EMA [31].

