#### Timelines and milestones

The recruitment period will be 36 months. The end of the study for all cohorts, except the pediatric cohort, will happen after the final patient has been in the study for at least 24 months or is no longer under observation, owing to being lost to follow-up, withdrawal, or death. For the pediatric cohort, each patient will be followed up for at least 60 months from larotrectinib initiation unless the patient is discontinued due to loss to follow-up, withdrawal, or death.

The study will be closed 60 months after the last pediatric patient has started treatment with larotrectinib or when no patient is still under observation due to loss to follow-up, withdrawal, or death. For all patients still under observation at time of study closure, a last disease status documentation will be required along with the completion of the final information collection.

Safety reviews will be performed annually, with the first review starting 1 year after the first patient is enrolled. Interim reviews for safety and effectiveness will be performed after approximately 50 patients pooled across tumor types complete at least 6 months of treatment or discontinue treatment. Subsequent reviews will be performed after approximately 150 and 300 patients have met the same conditions. In addition, reviews by cohort type will be performed after approximately 10 patients per cohort complete at least 6 months of treatment or discontinue treatment. The various reviews may be combined if they are expected to occur within approximately 1 month of each other.

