## Conclusion

The approval of larotrectinib in more than 40 countries marks not only a milestone in its development but also in the development of tumor-agnostic approvals. Ongoing clinical trials have shown positive efficacy and safety results. The aim of the ON-TRK non-interventional study is to investigate the effects of larotrectinib in a broader patient population in real-world clinical practice conditions and determine the impact of larotrectinib use on development in pediatric patients followed for at least 5 years from the initiation of larotrectinib.

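### The Discussion ends pediatric growth, milestone and neurological assessment when larotrectinib stops, while the Methods follow every child for at least 60 months from initiation

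*Protocol article*

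**What the plan says.** Two rules govern how long children are observed.

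- **Discussion**, in the text on the FDA post-approval requirements: patients are assessed for age-appropriate growth and milestones and examined neurologically, for example every six months, "until larotrectinib is discontinued or for at least 5 years, whichever occurs first".
- **Methods, Timelines and milestones**: for the pediatric cohort, "each patient will be followed up for at least 60 months from larotrectinib initiation". Only death, withdrawal and loss to follow-up are listed as exceptions. The same section adds: "The study will be closed 60 months after the last pediatric patient has started treatment with larotrectinib", or earlier if nobody remains under observation.

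Two other places agree with the Methods on length. The Abstract says that children "will be followed for 5 years to evaluate the risk of potential long-term adverse effects of larotrectinib on their growth and development". The Conclusion speaks of "pediatric patients followed for at least 5 years from the initiation of larotrectinib". The Methods and the Conclusion count the period from initiation; the Abstract names no starting point.

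The analysis of secondary variables summarizes pediatric height and weight change at each visit and does not restrict this to time on drug. Table 2 lists long-term growth, milestones and sexual development as a secondary objective in children, and long-term neurologic outcomes as a secondary objective in all patients.

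**The concern.** Under the Discussion rule, a child who stops larotrectinib at month 8 has a last growth, milestone and neurological assessment at about month 8. Under the Methods rule the same child is followed to month 60. A site could comply with one and breach the other.

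The Discussion rule is also hard to apply as worded. A minimum of five years is not a time point, so it cannot properly be one of two events of which the earlier counts.

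Two things are at stake for the pediatric objective. Effects that appear or persist after treatment would not be seen in children who stop early. And the children contributing at year 5 would be only those still taking the drug. They are a selected group, because a child who stopped for any reason, such as toxicity, progression or surgery, is no longer measured. A year-5 summary would then describe long-term users rather than children who started larotrectinib.

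**Working it through.** **1. Do the texts conflict?**

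| Place | Length for children | Ended by stopping the drug? |
|---|---|---|
| Abstract, Methods | 5 years, for growth and development | Not stated |
| Timelines and milestones | At least 60 months from initiation | Not among the listed reasons |
| Discussion | Earlier of discontinuation and (at least) 5 years | Yes |
| Conclusion | At least 5 years from initiation | Not stated |

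The Discussion alone makes discontinuation an end point. No other section restores these assessments after treatment stops.

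**2. How much would be lost under the Discussion rule?** The plan gives no figure to reproduce on this point. Its one computed figure, the 95% chance of seeing at least one event among 300 patients at 1% incidence, is correct (1 − 0.99^300 = 0.951) but does not bear on it.

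The article gives no median pediatric treatment duration for ON-TRK. For the earlier trials it gives only a range: "With the duration of treatment ranging from 1.3 + to 34.0 + months". An illustration therefore needs an assumption. I take time on drug to be exponential with median m months, and ignore loss, withdrawal and death.

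- Share still assessed at month 60 = 0.5^(60/m).
- Mean assessed time within the 60 months = (1 − 0.5^(60/m)) / (ln 2 / m).

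For m = 24, the share is 0.5^2.5 = 0.177 and the mean is (1 − 0.177) / 0.02888 = 28.5 months.

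| Assumed median (months) | Share assessed at month 60 | Mean assessed time (months) |
|---|---|---|
| 12 | 3.1% | 16.8 |
| 24 | 17.7% | 28.5 |
| 36 | 31.5% | 35.6 |
| 60 | 50.0% | 43.3 |
| 120 | 70.7% | 50.7 |

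Under the Methods rule, discontinuation removes nobody: the share is 100% and the time 60 months, before loss, withdrawal and death. Even with a ten-year median, the Discussion rule would forgo 100 − 70.7 = 29.3% of the year-5 assessments.

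**The case against.** The best defense is that the operative plan is in the Methods, which are sound. One sentence in the Discussion differs. It stands among sentences on the FDA requirements and may paraphrase them. The full protocol is not shown, so whether children would in fact stop being assessed cannot be known. That stands: what is established is a conflict of wording, not a loss of data that has occurred or is certain to occur.

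A second defense is that follow-up and serial examination are different things, so survival and disease status could be followed for 60 months while examinations stop with the drug. This does not reconcile the texts, because the Abstract gives growth and development as the purpose of the five pediatric years.

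Third, the size depends on the assumed median. This also stands. The pediatric data in the Background point both ways: a 92% response rate with median response duration and PFS not reached suggests long treatment, while resection after a median of six cycles in five children suggests short treatment.

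Stronger readings are tempting but go beyond the documents:

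- *All 5-year pediatric data would disappear.* Only children who stop before month 60 would lack them.
- *The study exists to collect these data.* The primary objective is treatment-emergent adverse events; growth and development is secondary.
- *No child stays on treatment for 60 months.* The plus sign on the 34.0-month maximum is unexplained. If it marks ongoing treatment, the maximum reflects the data cut.
- *A specific number of children would reach year 5.* That would also need the pediatric share of ON-TRK, which the article does not give. The 33% in the earlier dataset comes from non-CNS tumors, while ON-TRK also enrolls CNS tumors.

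**Conclusion.** The contradiction is real and should be removed. The Discussion states an end to growth, milestone and neurological assessment that the Methods do not allow for children and that does not serve the purpose given in the Abstract. It is a rule stated wrongly in one place, not a detail left to a fuller document.

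If the rule were followed, the share of children still assessed at month 60 would run from 3.1% to 70.7% for assumed median treatment times of 12 to 120 months. Those figures rest on an exponential model and on medians that the article does not supply. They show the direction and possible scale of the loss, not an expected yield. The bias does not depend on the model: at year 5, only children still on drug would be described.

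The point affects a secondary objective and a stated regulatory requirement. The primary safety objective is untouched.

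**What to change.** 1. Reconcile the Discussion with Timelines and milestones. For the pediatric cohort, state once that the growth, milestone and neurological assessment window is the 60 months from initiation already in the Methods, whatever the treatment status.
2. Delete "until larotrectinib is discontinued or for at least 5 years, whichever occurs first" from the Discussion.
3. State separately the window for neurological outcomes in adults, consistent with their own follow-up. The Discussion sentence refers to patients in general and the neurologic objective covers everyone, but the 60 months apply to children only.
4. Summarize pediatric growth and development by time since initiation, distinguishing time on drug from time off drug. The detail can sit in the analysis plan.

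These changes concern data collection, not treatment.

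The wording change costs little. The real cost is some added data collection after discontinuation, in children the plan already follows. The documents do not give its size. Examinations follow the local label and standard of care, so it cannot be assumed that neurological or Tanner assessments are routine once the drug has stopped. Early correction helps: 22 of up to 300 patients had been enrolled by November 2021, and an assessment not made when due may not be recoverable.

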## Conclusion

The approval of larotrectinib in more than 40 countries marks not only a milestone in its development but also in the development of tumor-agnostic approvals. Ongoing clinical trials have shown positive efficacy and safety results. The aim of the ON-TRK non-interventional study is to investigate the effects of larotrectinib in a broader patient population in real-world clinical practice conditions and determine the impact of larotrectinib use on development in pediatric patients followed for at least 5 years from the initiation of larotrectinib.

## Data Availability

Not applicable.

## Abbreviations

AE: Adverse event
CI: Confidence interval
CNS: Central nervous system
CTCAE: Common Terminology Criteria for Adverse Events
DCR: Disease control rate
DOR: Duration of response
EMA: European Medicines Agency
FDA: US Food and Drug Administration
FISH: Fluorescence in situ hybridization
GVP: Good pharmacovigilance practices
IHC: Immunohistochemistry
IRC: Independent review committee
MedDRA: Medical Dictionary for Regulatory Activities
NCI: National Cancer Institute
NGS: Next-generation sequencing
*NTRK*: Neurotrophic tyrosine receptor kinase
ORR: Objective response rate
OS: Overall survival
PFS: Progression-free survival
RT-PCR: Reverse-transcription polymerase chain reaction
SAE: Serious adverse event
TEAE: Treatment-emergent adverse event
TRK: Tropomyosin receptor kinase
TTR: Time to response
